### Study eligibility criteria

Individuals of any age with a diagnosis of intellectual disability (ICD-10 code F7x) or autism (ICD-10 code F84) will be identified using diagnostic information entered into structured fields or in the free text record using the NLP diagnosis application. Participants must have a recorded diagnosis of intellectual disability and/or autism. Eligible participants must have received an episode of care from a community mental health service provided by SLaM for at least one continuous year between 1 January 2015 and 31 December 2023 to ensure that sufficient data are held in the record. All eligible episodes of care will be included, including those individuals with more than one period of community care of at least 1 year during this timeframe.

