## Abstract

**Abstract:**

**Introduction:**

Care (Education) and Treatment Reviews (C(E)TRs) are intended to reduce unnecessary psychiatric hospital admission and length of stay for people with intellectual disability and autistic people. The use and impact of C(E)TRs have not been systematically evaluated since their introduction in England in 2015. The aims of this study are to describe the demographic and clinical profiles of people who receive a community C(E)TR and to investigate their effects on admission, length of hospital stay and clinical and functional change.

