**Methods and analysis:**

We will conduct a retrospective cohort study using de-identified data from electronic health records derived from two large National Health Service mental health providers in London, England, including one replication site. Data will be extracted using the Clinical Record Interactive Search (CRIS) tool for all people with recorded intellectual disability and/or autism who received mental healthcare from 2015. We will identify community C(E)TR events using keyword searches. Community C(E)TRs will be examined in two ways: (1) In a community cohort, we will capture data in the 6-month periods before and after a community C(E)TR and compare this to a matched control group and (2) In a hospital cohort, we will compare groups who did and did not receive a community C(E)TR prior to their admission. We will describe the socio-demographic and clinical profiles of each group and their health service use, and compare C(E)TR and no C(E)TR groups using t-tests (or a non-parametric equivalent). The primary outcomes are admission to a psychiatric hospital (community cohort) and length of psychiatric hospital admission and clinical change (hospital cohort). Admission to psychiatric hospital will be estimated using propensity score weighting and difference-in-differences methods. Cox’s proportional hazard model will be used for length of hospital admission and repeated-measures analysis of variance (ANOVA) will be used to assess clinical change.

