**Ethics and dissemination:**

Use of CRIS to examine de-identified clinical data for research purposes has overarching ethical approval. This study has been granted local approval by the South London and Maudsley CRIS Oversight Committee. Findings will be disseminated in an open-access peer-reviewed academic publication, at conference presentations, and to service users and carers in accessible formats.

STRENGTHS AND LIMITATIONS OF THIS STUDYThis study uses routinely collected health data, which represent real-world clinical practice and enables us to generate a relatively large cohort not biased by participant selection.The study will be undertaken in a large NHS Trust with a diverse catchment area.We will replicate the study in a second NHS Trust to provide evidence for the generalisability of the initial findings across a different population.The number of people in the dataset who have received a community Care (Education) and Treatment Review is unknown; if there are relatively few events, our dataset may be underpowered to demonstrate differences between those who do and do not receive the intervention (type 2 error).Electronic health record data are generated as part of routine clinical practice and may include missing data, which could limit our analysis.

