#### Sub-study 1: community cohort

We will: (1) Examine the demographic and clinical profile of those who receive a community C(E)TR and (2) attempt to model the causal relationship of receiving a community C(E)TR on the risk of psychiatric hospital admission.

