### Identification of C(E)TRs

We will undertake keyword searches in the EHR of people with intellectual disability or autism who meet the study eligibility criteria to identify each community C(E)TR event and the date on which it occurred. Search terms will be ‘Care and Treatment Review’, ‘Care Education and Treatment Review’, ‘CTR’ and ‘CETR’. The search interface does not recognise punctuation or wildcards. We will create a list of people whose health records contain any of these text strings and will review the context of the positive mention to ascertain true instances of C(E)TR meetings, along with the date that the meeting was held. We will label a C(E)TR meeting as having taken place where there is evidence that a meeting has occurred and where a date of the meeting is available. We expect there will be mentions of the search terms which do not correspond to a C(E)TR meeting taking place, for example, where a possible future C(E)TR is flagged. Some mentions of the search terms will be false positives (eg, spe*ctr*um, ECG), and such irrelevant cases will be discounted.

To ensure reliability of identification, two members of the research team will independently review records of 100 eligible patients where C(E)TR search terms have been identified. Cohen’s Kappa will be calculated to test the agreement between the two raters.^10^ If inter-rater reliability is acceptable (Cohen’s kappa >0.6), the raters will work independently and only flag cases that cannot easily be determined. If initial inter-rater reliability is inadequate (Cohen’s kappa <0.6), we will discuss and refine the method of ascertaining whether a keyword mention represents a C(E)TR meeting using a series of test cases. The raters will reconvene periodically to double-review a subset of records to ensure that practice remains consistent. We will retain key excerpts of anonymised text from the EHR as exemplars of mentions of C(E)TRs; a selection of these will be reported for transparency, and the examples can also be used to train any additional members of the research team who interrogate the records.

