### Sensitivity analyses

Sensitivity analyses will be carried out on the causal framework to probe the robustness of the applied model. During the C(E)TR identification process, we will identify patients for whom a community C(E)TR was suggested, where there was no evidence that a C(E)TR did in fact occur. These are to be included in the pool of control patients in our main analysis. Exploratory sensitivity analyses will: (1) Re-assign these patients to the C(E)TR group, and use the date in the record when a C(E)TR was suggested (or soon thereafter) as the index date and/or (2) Directly compare the main C(E)TR group with the ‘C(E)TR suggested’ group.

Some patients may have multiple community C(E)TRs while under follow-up. These will be treated as separate events in the main analysis (if the C(E)TRs are at least 6 months apart). Patients who have multiple C(E)TRs may have a different profile of baseline characteristics than those who receive only one. This may lead to preintervention differences in the C(E)TR versus no C(E)TR groups that cannot be sufficiently controlled for using the propensity scoring method. A sensitivity analysis will be performed on the subgroup of patients who only had one C(E)TR (vs no C(E)TR), improving sensitivity to the causal effect of a single C(E)TR.

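### The profile of people who receive a community C(E)TR leaves out recipients without a continuous year of community care and, as written, counts reviews rather than people

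*Protocol article*

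**What the plan says.** The protocol article states its first aim without restriction. The abstract's introduction says the study will "describe the demographic and clinical profiles of people who receive a community C(E)TR", and the sub-study 1 aims repeat it: "Examine the demographic and clinical profile of those who receive a community C(E)TR". The abstract's methods paragraph says data are extracted "for all people with recorded intellectual disability and/or autism who received mental healthcare from 2015". The strengths and limitations box says that routine data "enables us to generate a relatively large cohort not biased by participant selection".

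*Study eligibility criteria* then admits only people under a SLaM community service "for at least one continuous year between 1 January 2015 and 31 December 2023 to ensure that sufficient data are held in the record". It adds: "All eligible episodes of care will be included". *Identification of C(E)TRs* confines the keyword search to "people with intellectual disability or autism who meet the study eligibility criteria". Table 1 and *Matching a control group* repeat the one-year condition.

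Under *Descriptive measures*, the baseline variables (age, sex, ethnicity, deprivation and other indicators) are taken at the index date, which is the date of a review. Under *Multiple C(E)TRs*, reviews more than 6 months apart in one patient are separate events. *Sensitivity analyses* remarks: "Patients who have multiple C(E)TRs may have a different profile of baseline characteristics than those who receive only one".

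**The concern.** Eligibility is applied before reviews are looked for. A person whose community care never reached a continuous year, for example someone who was reviewed soon after referral and then moved away or died, is outside the search. The study will not describe such recipients and cannot say how many there were. Neither the listed limitations nor the sensitivity analyses mention this.

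The table of recipients is also built from index dates, of which one person may have several. A table of reviews answers a different question from a table of people, and the protocol itself expects repeat recipients to differ.

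The Introduction says that knowing who does and does not receive a review may help to target work on access. People with brief or interrupted care are relevant to that purpose, and they are the group the rule removes.

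**Working it through.** The plan states no figure on this point, so there is nothing to reproduce. The check traces the order of selection and then shows what size of effect is possible.

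**1. Order of selection.** Diagnosis, then one continuous year of community care in 2015–2023, then the keyword search, then classification as community or inpatient, then the descriptive tables. The year is imposed two steps before a community review is established. No later step brings back anyone removed there.

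**2. Does the stated reason fit the data needed?** The reason given is that enough data be held in the record.
- Socio-demographic profile: measured at the index date. A year of care is not needed.
- Clinical and service-use description: 6 months before plus 6 months after, which is 12 months. A year of care is a plausible requirement here.
- The year is not tied to the review date. Suppose a person has a single 12-month episode and is reviewed one month into it. That person qualifies with 1 of the 6 pre-review months under care. Inclusion required 12 − 1 = 11 further months of care after the review.

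So the rule does not guarantee pre-review data, and for early reviews it makes inclusion depend on what happens afterwards.

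**3. Who is missed.** The search works on people. Someone with a short spell and a separate qualifying year is still searched. Whether a review held in the short spell would count is unclear, because only eligible episodes are included. Exclusion is certain only for people with no qualifying year at all.

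**4. Possible size of the exclusion effect (assumed inputs).** Let s be the share of all recipients excluded and d the difference in a characteristic, in percentage points, between included and excluded recipients. The percentage among all recipients is (1 − s) × included + s × excluded, so the reported (included) figure is off by s × d.

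| s | d = 10 points | d = 20 points |
|---|---|---|
| 5% | 0.5 | 1 |
| 10% | 1 | 2 |
| 20% | 2 | 4 |
| 30% | 3 | 6 |
| 40% | 4 | 8 |

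**5. Possible size of the repeat-counting effect (assumed inputs).** Suppose 20% of recipients average 2.5 reviews, the rest have one each, and a feature is present in 60% of the former and 30% of the latter.
- Rows per recipient: 0.8 × 1 + 0.2 × 2.5 = 1.3.
- Share of rows from repeat recipients: 0.5 / 1.3 = 38.5%, against 20% of people.
- Prevalence per person: 0.8 × 30% + 0.2 × 60% = 36%.
- Prevalence per row: (0.8 × 30% + 0.5 × 60%) / 1.3 = 41.5%.
- Difference: 5.5 points.

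None of the inputs to steps 4 and 5 is in the document, which says that the number of recipients is unknown.

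**The case against.** The strongest reply is that the rule is openly stated and has a purpose. The aim covers the clinical as well as the demographic profile, and Table 1 lists symptoms, clinical variables and service use in two 6-month windows. Variables from natural language processing are coded as any mention within a surveillance period, so a short record would tend to read as absence. This stands for the clinical windows and for the comparison with controls, who must meet the same rule. It does not extend to age, sex, ethnicity and deprivation at the index date.

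A reader might infer that the article passes off a selected cohort as unselected. The text does not support that. The one-year rule appears in the eligibility criteria, Table 1 and the control criteria. An abstract condenses, and the strength is tied to routine data, so its natural meaning is freedom from volunteer or recruitment bias. What remains is that the abstract and the eligibility section do not match and that the restriction is not listed as a limitation.

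On repeat counting, it can be said that the article does not explicitly choose rows or persons and that such detail is often left to an analysis plan. That has some force. But the sections on index date, descriptive measures and multiple reviews together lead to one row per review, and the planned analysis of patients with a single review belongs to the causal framework, not to the descriptive tables.

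It is also fair that recipients with short care would have no like-for-like controls. That argues for describing them separately, not for leaving them uncounted.

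**Conclusion.** The concern holds in a limited form. The descriptive aim is stated for people who receive a community review. The procedure delivers a profile of reviews in people with at least one continuous year of community care. Recipients with no qualifying year are not found, and repeat recipients weigh more than once in the baseline table as written.

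The size of either effect cannot be derived from the document. On the assumed values above, the exclusion effect runs from 0.5 to 8 points and the repeat-counting example gives 5.5 points. Both could be negligible if few recipients have short care or repeat reviews.

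Two stronger readings are not supported. One is that everyone reviewed in a short spell or a first crisis is lost; such a person is still searched if a qualifying year exists anywhere in 2015–2023. The other is that the one-year rule is unjustified throughout; it is defensible for the matched and difference-in-differences analysis and the before/after windows. The point bears on the first aim and on how its population is described.

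**What to change.** Keep the one-year rule for the matched and difference-in-differences analysis and for the before/after descriptions. For the descriptive aim only:

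1. Run the keyword search in all people with a recorded diagnosis and any SLaM community care in the period.
2. Report the number and basic socio-demographic profile of recipients outside the one-year rule, without a control comparison.
3. Add a table counting each recipient once, at the first community C(E)TR.

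The cost is more keyword-positive records to check by hand, a number the document does not allow one to estimate, and one or two extra descriptive tables. The causal analyses do not change.

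If the search cannot be widened, still add the per-person table. Then align the abstract with the eligibility criteria, limit the stated aim and conclusions to people with at least one continuous year of community care, list this as a limitation, and qualify the stated strength as freedom from volunteer or recruitment bias. Apart from one table from data already extracted, this alternative needs only changes of wording.

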### Identification of C(E)TRs

We will undertake keyword searches in the EHR of people with intellectual disability or autism who meet the study eligibility criteria to identify each community C(E)TR event and the date on which it occurred. Search terms will be ‘Care and Treatment Review’, ‘Care Education and Treatment Review’, ‘CTR’ and ‘CETR’. The search interface does not recognise punctuation or wildcards. We will create a list of people whose health records contain any of these text strings and will review the context of the positive mention to ascertain true instances of C(E)TR meetings, along with the date that the meeting was held. We will label a C(E)TR meeting as having taken place where there is evidence that a meeting has occurred and where a date of the meeting is available. We expect there will be mentions of the search terms which do not correspond to a C(E)TR meeting taking place, for example, where a possible future C(E)TR is flagged. Some mentions of the search terms will be false positives (eg, spe*ctr*um, ECG), and such irrelevant cases will be discounted.

To ensure reliability of identification, two members of the research team will independently review records of 100 eligible patients where C(E)TR search terms have been identified. Cohen’s Kappa will be calculated to test the agreement between the two raters.^10^ If inter-rater reliability is acceptable (Cohen’s kappa >0.6), the raters will work independently and only flag cases that cannot easily be determined. If initial inter-rater reliability is inadequate (Cohen’s kappa <0.6), we will discuss and refine the method of ascertaining whether a keyword mention represents a C(E)TR meeting using a series of test cases. The raters will reconvene periodically to double-review a subset of records to ensure that practice remains consistent. We will retain key excerpts of anonymised text from the EHR as exemplars of mentions of C(E)TRs; a selection of these will be reported for transparency, and the examples can also be used to train any additional members of the research team who interrogate the records.

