## Methods and analysis

### Study setting

Data will be obtained from the South London and Maudsley (SLaM) NHS Foundation Trust. SLaM is one of the largest providers of secondary mental healthcare in Europe, with a diverse catchment area of approximately 1.3 million people who live in the south London boroughs of Lambeth, Southwark, Lewisham and Croydon. Mental health services provided by SLaM include specialist teams for children and adolescents with mental illness and/or neurodevelopmental conditions, community teams for adults, including specialist teams for those with intellectual disability, and mainstream and specialist inpatient wards across different sites. The Trust has implemented a full EHR since 2006, and the SLaM NIHR Maudsley Biomedical Research Centre Case Register contains the clinical records of >5 00 000 patients.^4 5^ Unless otherwise stated, data will be extracted up to an end date of 31 December 2024. The protocol for this study was finalised in July 2025. Data extraction is anticipated to be complete by September 2025 and data analysis by December 2025.

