### Natural language processing

NLP is an information extraction technique used to identify relevant information from unstructured free text via automated methods.^8^ NLP models are developed by defining a construct of interest (eg, aggression) and manually annotating examples in a set of training data to classify true positive instances of the construct. Various clinically relevant NLP applications have been developed for use in the SLaM EHR.^9^ NLP-derived data in this study will be obtained as binary variables, which indicate the presence of at least one mention of the construct of interest within a given surveillance period.

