### Classification of C(E)TRs as community or inpatient

Information on all psychiatric inpatient spells will be extracted for those in the cohort. We will place this alongside the dates of recorded C(E)TRs to categorise the C(E)TR as a community C(E)TR (ie, occurring when the person was living in the community) or an inpatient C(E)TR (ie, occurring when the person was admitted to a psychiatric hospital). All analyses that follow will be performed on community C(E)TRs.

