### Identifying cases and controls

Using the review of clinical records of eligible patients previously described, we will measure whether each patient had a community C(E)TR within 6 months prior to their psychiatric hospital admission. We will form two groups: those who had a pre-admission community C(E)TR, and those who did not.

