### Missing data

The design of the study ensures that the intervention and outcome are fully observed; however, owing to the nature of the data source, we anticipate non-trivial proportions of missing confounder data. We will report the proportion and frequency of missing values for covariates. We will consider the missingness pattern approach, a technique which, if key assumptions are not violated, retains all people in the analysis. We will undertake various sensitivity analyses to explore whether our conclusions are affected when the assumption for the missing pattern approach is violated.^21^ A similar approach will be applied to the economic analysis, where missing data will be addressed using multiple imputation by chained equations with predictive mean matching.^22^

### Extensions of sub-study 1 and sub-study 2

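### The C(E)TR search is not limited to text written before the outcome, so exposure may be detected more often in people who are admitted or stay longer

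*Protocol article*

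**What the plan says.** Under Identification of C(E)TRs, the search covers the record of every eligible person ("We will undertake keyword searches in the EHR of people with intellectual disability or autism who meet the study eligibility criteria"), and "We will create a list of people whose health records contain any of these text strings". The raters then judge each mention: "We will label a C(E)TR meeting as having taken place where there is evidence that a meeting has occurred", provided that a meeting date is available. Nothing is said about when, or in which setting, the supporting text must have been written. Under Study setting, "data will be extracted up to an end date of 31 December 2024", one year after the eligibility window closes on 31 December 2023.

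Classification of C(E)TRs as community or inpatient goes by meeting date. Inpatient spells are extracted, and "We will place this alongside the dates of recorded C(E)TRs". Sub-study 2 takes over the same review (Identifying cases and controls): "Using the review of clinical records of eligible patients previously described".

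Two contrasts matter. Variables derived by natural language processing are windowed: they record the "presence of at least one mention of the construct of interest within a given surveillance period". The exposure has no such window. And the Missing data section states: "The design of the study ensures that the intervention and outcome are fully observed".

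**The concern.** Admission adds text to the record, and a longer stay adds more. Some of that text can recount what happened before admission. The Introduction also notes that inpatient C(E)TRs take place at various points of a stay, so admission itself generates the search terms that put a person on the review list. A community C(E)TR poorly documented at the time could then be recovered from ward or discharge notes in someone who was admitted. The same C(E)TR in someone never admitted has no such route, and that person counts as unexposed.

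If this happens, the chance of being classed as exposed depends on the outcome. The bias would then make C(E)TRs look linked to more admission in sub-study 1 and to longer stay in sub-study 2, and could hide a real benefit. It cannot be assessed afterwards unless the dates of the source notes are captured during the review.

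**Working it through.** The protocol gives no detection rates, event counts or expected effect, so there is no stated figure to reproduce. The calculations below only show how the size depends on assumed detection, with a true effect of nil throughout.

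**Sub-study 1.** Let p be the true 6-month admission risk, s1 the chance that a real C(E)TR is found if the person is later admitted, and s0 the chance if not.

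- Observed risk in those classed as exposed = p·s1 / [p·s1 + (1−p)·s0]. The odds are multiplied by s1/s0.
- Observed risk in controls, if a fraction q of the control pool truly had a C(E)TR before detection = p·A / [p·A + (1−p)·B], where A = (1−q) + q(1−s1) and B = (1−q) + q(1−s0).

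Assumed p = 0.20 and q = 0.05. Worked case, s0 = 0.80 and s1 = 0.95:

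- exposed: 0.19 / (0.19 + 0.64) = 22.9%
- controls: 0.1905 / (0.1905 + 0.768) = 19.9%

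| s0 | s1 | Exposed | Controls | Difference (points) | Odds ratio |
|---|---|---|---|---|---|
| 0.90 | 0.90 | 20.0% | 20.0% | 0.0 | 1.00 |
| 0.90 | 0.95 | 20.9% | 20.0% | +0.9 | 1.06 |
| 0.80 | 0.95 | 22.9% | 19.9% | +3.0 | 1.20 |
| 0.60 | 0.90 | 27.3% | 19.8% | +7.5 | 1.52 |

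Incomplete detection alone does no harm here (first row). What matters is that s1 exceeds s0.

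These are crude contrasts, not the planned weighted difference-in-differences estimate. That method does not in general remove the problem: notes written before a C(E)TR cannot show that it took place, so only post-index admissions add chances of detection. Subtracting the pre-index difference helps only so far as earlier and later admissions go together.

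**Sub-study 2.** Simulated model: stay = 14 days plus an exponential with mean 60 days; 25% truly exposed; follow-up censored at 182 days. A share d0 of C(E)TRs is found in pre-admission notes, and each month in hospital recovers a fraction k of those still unfound. Each month after discharge recovers a fraction f·k, counted up to an assumed 12 months from admission. The chance of detection is 1 − (1−d0)(1−k)^(months in hospital)·(1−f·k)^(months after discharge). A Cox model for discharge was fitted to 2,000,000 simulated stays, with a standard error of the log hazard ratio of about 0.002.

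| d0 | k | f = 0 | f = 1/3 | f = 1/2 | f = 1 |
|---|---|---|---|---|---|
| 0.6 | 0.20 | 0.88 | 0.95 | 0.97 | 1.00 |
| 0.7 | 0.15 | 0.92 | 0.97 | 0.98 | 1.00 |
| 0.8 | 0.15 | 0.95 | 0.98 | 0.99 | 1.00 |
| 0.8 | 0.10 | 0.96 | 0.98 | 0.99 | 1.00 |

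For d0 = 0.7 and k = 0.15 with f = 0, detection rises from 72% at 14 days to 89% at 182 days. With complete detection the hazard ratio is 1.00. Because extraction runs to the end of 2024, f = 0 is the extreme case: notes written after discharge are searched as well.

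**Planned safeguards.** Cohen's kappa uses 100 records that already contain a search term. It measures agreement between raters, not missed C(E)TRs or their dependence on outcome. Propensity weighting balances baseline covariates and does not touch detection. The sensitivity analysis that reassigns people with a suggested but unconfirmed C(E)TR addresses under-recording only where a suggestion was noted.

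**The case against.** The strongest reply is that differential detection is a hypothesis. It needs community notes to miss C(E)TRs and ward notes to supply dated confirmation, and the protocol gives evidence of neither. Several features point to recording at the time: each C(E)TR yields a report and action plan, participants have at least a year of community care, and sub-study 2 patients were open to a community team for 6 months before admission. An undated recollection in a ward note does not qualify. People who are not admitted also go on accruing notes. All of this stands. It limits the likely size but does not close the route.

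A reader might infer more than the text supports:

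- That the protocol says ward notes will be used. It does not; this follows from an unrestricted search.
- That raters will know the outcome. The article is silent on masking, and abstraction detail of that kind is commonly left to a fuller document.
- That the Missing data statement claims perfect detection. It is made in contrast to missing confounder values and need not mean that.
- That no planned analysis bears on under-recording. The suggested-C(E)TR reassignment does in part.

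It can also be objected that making a restricted definition the main analysis would knowingly misclassify confirmed C(E)TRs when events may already be few. That is a fair objection, and it is why the change proposed here is a sensitivity analysis.

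**Conclusion.** The concern holds as a gap in the exposure definition, not as a demonstrated bias. Qualifying text has no time limit and classification rests on meeting date alone, so notes from the outcome admission onwards can establish exposure in both sub-studies. If community recording is incomplete and admission adds detections, the bias runs towards more admission and longer stay.

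Its size is unknown. Under the assumed rates it ranges from negligible to an odds ratio of about 1.5 in sub-study 1. In sub-study 2 the hazard ratio for discharge ranges from 0.88 to 1.00, and shrinks towards 1 as notes after discharge also recover C(E)TRs. It is zero if community notes are complete. The documents do not support saying that exposure is in fact found more often in those admitted, nor that the main definition must be replaced. They also do not assure that the intervention is fully observed. The point is worth acting on because the fix is cheap and the information cannot be recovered unless it is collected during the review.

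**What to change.** 1. During the planned review, record the entry date and source (community or inpatient) of the earliest text that establishes each C(E)TR.
2. Report how many C(E)TRs rest only on text written after the outcome admission began.
3. Add a sensitivity analysis in both sub-studies with a restricted exposure definition. In sub-study 2, count only C(E)TRs established by entries dated on or before the admission date. In sub-study 1, count only those established by non-inpatient entries within a fixed period after the meeting, the same for everyone. Excluding inpatient entries is needed because an early admission would otherwise still put ward notes inside that period.
4. Reword the Missing data statement to say that exposure is ascertained from recorded text and may be incomplete.

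The cost is one or two extra fields in a review already planned, and one repeat analysis. In that analysis some true C(E)TRs are classed as unexposed, especially those held just before an admission, which have little time to be written up. It should therefore be read beside the main analysis and not as a replacement. Close agreement would be reassuring; a marked shift would limit what can be concluded.
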